### Recruitment process

Recruitment commenced in August 2009. Medical records were screened for contraindications to physical activity [47] by a general practitioner. Computer random sequence generation was used to determine the order of screening. Recruitment was via letter sent from a general practitioner. Individuals were asked to indicate on a reply slip whether they would be interested in taking part. Positive responders indicated their preferred method of contact (email, post or telephone). A researcher contacted those wishing to take part to assess current physical activity participation and to schedule the first appointment. An open-ended question for negative responders to provide a reason why they did not want to take part was included in the recruitment letter. Reminder letters were sent out at least two weeks after initial study invitations to individuals that did not respond to the initial recruitment letter. Negative responders who did not give a reason for declining participation in their first reply were sent a further letter asking for help in trying to understand why the study did not appeal to them to assist the research team with future study recruitment.

### Study population

Inclusion criteria were as follows: aged ≥65 years; able to understand the study rationale; living independently; English speaking and not meeting the current physical activity recommendations (defined as being in the pre-contemplation, contemplation or preparation stages of change from the Transtheoretical Model of behaviour change in relation to meeting the current physical activity recommendations [48] (see table 1 for descriptions)). After discussion with a researcher on the telephone, individuals who were already regularly physically active (e.g. in stage 4 or 5) were excluded from the study. Two participants recruited into the study were from the same household (the second member of the household was not invited into the study until the first member had completed participation in the study).

**Table 1 T1:** Description of the stages of change in relation to meeting the current physical activity recommendations

Stage	Stage name	Description of individual in terms of physical activity participation
1	Pre-contemplation	Not regularly physically active and do not intend to be in the next 6 months
2	Contemplation	Not regularly physically active but are thinking about becoming more active in the next 6 months
3	Preparation	Do some physical activity but do not participate in regular physical activity
4	Action	Regularly active but for less than 6 months
5	Maintenance	Regularly active for over 6 months

### The intervention

Glasziou and colleagues [49] highlight the importance of fully describing intervention protocols in enough detail for others to replicate the intervention. The authors acknowledge that full reporting may not be feasible in scientific journals where space is limited and thus recommend providing links to websites where full details are available [49]. Intervention pro formas for this study are detailed in the intervention manual which can be accessed at http://www.strath.ac.uk/humanities/courses/physicalactivityforhealth/staff/[name]/ or by contacting the chief investigator. A 30 minute physical activity consultation was delivered individually to each participant by a practice nurse who had been trained in consultation procedures. To examine delivery of the intervention by a practice nurse and to assess consultation fidelity, audio recordings of consultations were made. NHS Health Scotland has provided physical activity consultation training which can be undertaken by anyone with an interest and basic knowledge in health and physical activity (i.e. college or university level knowledge is not required) and is delivered over 1-2 days. The lead trainer for these courses conducted a one-to-one training session with the study practice nurse over 1 day and was available for clarification and guidance as the nurse practiced these skills before delivering a consultation with participants. The consultations followed recommended guidelines [24], were based on the social cognitive model of behaviour change as a theoretical framework, and have previously been shown to successfully increase physical activity participation in adults [17,50,51]. Details of the behaviour change processes targeted in the consultations are provided in Table 2. The intervention involved two consultations. The aim of the initial consultation was to increase walking participation. A second consultation focussed on relapse prevention (12 weeks after the first consultation) and aimed to maintain walking behaviour.

**Table 2 T2:** Description of the behaviour change techniques targeted in the consultations

Behaviour change technique	How the technique was used in the consultation
Motivation for taking part	Discussion of why participant interested in the project
Information on the link between walking and health	Reflection on role of physical activity for health and well being
Self reflection on pros and cons of increasing walking	Weighing up pros and cons of increasing walking
Graded tasks	Graded walking goals set tailored to each individuals baseline pedometer readings
Instruction	Using the pedometer
Self-monitoring	Using the pedometer to monitor progress towards goals
Identifying and overcoming barriers	Recognising barriers and inviting participant to consider ways to overcome
Relapse prevention	For immediate intervention group only at consultation two: discussion of avoiding lapses, recognising situations which make walking difficult, thinking of alternatives.

A 12-week individualised walking programme and pedometer were also given to participants. Details of the walking programme are given in Table 3. A cadence of 100 steps/minute has become a widely-accepted population guideline for an adult walking at a moderate pace, and has been confirmed in two recent controlled studies of overground walking [52,53]. Thus increasing step count by 3,000 steps/day equates to approximately 30 minutes of moderate intensity physical activity. It is important to note however that limited research has examined step rate specifically in older adults with only one of these studies including adults aged 50-65 years [53].

**Table 3 T3:** Details of the 12-week pedometer based graduated walking programme

Week	Goal
Week 1-2	To increase the individual's average daily step count by 1500 steps above their baseline value on at least 3 days of the week
Week 3-4	To increase the individual's average daily step count by 1500 steps above their baseline value on at least 5 days of the week
Week 5-6	To increase the individual's average daily step count by 3000 steps above their baseline value on at least 3 days of the week
Week 7-8	To increase the individual's average daily step count by 3000 steps above their baseline value on at least 5 days of the week
Week 9-12	To maintain their walking level aiming for the week 7 goal

A local walking group was set up and led by a trained walk leader to help participants increase walking participation by providing peer support and a social support network. Feedback from participants in the WWW trial suggested the provision of a local walking group would have enhanced the study [23]. Paths for All (http://www.pathsforall.org.uk), a national charity which promotes walking for health, assisted in the establishment (including the training of walk leaders by completion of a one day course) and sustainability of the walking group. An attendance record was kept to determine how many participants used the group and how often.

### Design

There were two groups in the study; an immediate intervention group (immediate group) and a 12-week waiting list group (delayed group). The design of the study was a 12-week randomised controlled trial with a 12-week follow up for the intervention group. The immediate group received the intervention when they were entered into the study. The delayed group acted as a control group and were instructed to continue with their normal physical activity behaviour for the first 12 weeks of the study before receiving the same intervention as the immediate group.

### Procedures

Participants were invited to attend six study visits over 24 weeks (Figure 1). At visit 1, participants met with the practice nurse to go over the study protocol, discussed their present health with the general practitioner, completed informed consent and questionnaires and were fitted with a sealed pedometer (so that participants were unaware of their step counts before being given the intervention) and an *activ*PAL. All participants were instructed to continue with their normal physical activity patterns. At visit 2, one week after visit 1, individuals were randomised, on a one-to-one basis, into the immediate or delayed group by selecting a sealed envelope. Those who achieved ≥70,000 steps/week at baseline were classed as regularly physically active and excluded from participation as this equates to ≥150 minutes of moderate physical activity/week [54]. Participants in the delayed group were instructed at this visit to continue with their normal physical activity patterns for the next 12 weeks. At visit 3, 11 weeks after visit 1, all participants were fitted with an *activ*PAL and the immediate group continued to wear an unsealed pedometer (as they had had the intervention and were using the pedometer as part of the walking programme) whilst the delayed group were fitted with a sealed pedometer (because they were yet to receive the intervention). During visit 4, 12 weeks after visit 1, both groups completed 12-week questionnaires. Also at this visit the immediate group were given a second consultation whilst the delayed group were given an initial physical activity consultation, an individualised incremental 12-week walking programme and a pedometer (just as the immediate group had at visit 2). At visit 5, 23 weeks after visit 1, all participants continued to wear unsealed pedometers (as they had all started the walking programme) and were fitted with an *activ*PAL. All participants completed 24-week questionnaires and were given thank-you packs (consisting of information on local physical activity opportunities and a pedometer) at visit 6, 24 weeks after visit 1. In addition the delayed group were encouraged by the nurse to increase or maintain their walking levels based on whether the individual had met their target step goal over the previous 12 weeks or not. The practice nurse and a research assistant who conducted participant visits were not blinded to group allocation because they were providing the interventions. All participants' information and data were labelled with an identification number. All other researchers were blinded to group allocation.

**Figure 1 F1:**
[figure not shown]
**Flowchart of participant visits through the study**.

### Outcome measures

#### i) Physical activity

Daily physical activity was assessed using step counts measured by a sealed pedometer (NL-1000, New Lifestyles Inc, Lee's Summit, Missouri, USA). The NL-1000 records step count and minutes in moderate-to-vigorous intensity activity for the previous 7 days. Participants were instructed to wear the pedometer at all times apart from when washing and sleeping. The NL-1000 threshold for moderate-to-vigorous intensity was set at Level 3, corresponding to walking activity above 2.9 METs [55].

#### ii) Activity patterns

The *activ*PAL monitor (PAL technologies Ltd, Glasgow, Scotland) was used to assess activity in more detail. The *activ*PAL is a small (5 × 3.5 × 0.7 cm), light (20 g) unit which is attached to the anterior surface of the thigh, approximately midway between the inguinal crease and the proximal border of the patella. The monitor measures many variables including total time and percentage of time spent seated/lying, standing and walking, the duration of these events, number of steps per day and during each walking period and the cadence of walking periods. A detailed breakdown of the patterns of daily activity is given by the *activ*PAL as events and periods of time spent in particular postures are time stamped. Data were recorded in 15-second epochs. The *activ*PAL has a battery life of around 9 days and was worn continuously during this period (providing 8 full days of data). The monitor has previously been validated for use with an older population [56].

Physical activity and patterns of physical activity were measured at baseline, between 11 and 12 weeks and between 23 and 24 weeks in both groups over a period of 7-12 days (figure 1). At baseline pedometers were sealed using tape for both groups and at 11 weeks for the delayed group so that participants were not aware of their step counts. After the initial consultation (visit 2 for the immediate group and visit 4 for the delayed group) participants were given an unsealed pedometer. Pedometer and *activ*PAL data collected between visits 1 and 2 gave a baseline reading of physical activity participation for both groups. Between visits 3 and 4 for the immediate group and between visits 5 and 6 for the delayed group, pedometer and *activ*PAL data gave a measure of physical activity participation 12 weeks after the initial consultation. When physical activity was assessed between visits 5 and 6 for the immediate group this gave a measure of participation 12 weeks after the second consultation (i.e. 24 weeks after the initial consultation). Physical activity behaviour was also assessed subjectively using the Stage of Change question [48] at baseline and again at 24 weeks in both groups.

#### ii) Well-being

To determine the efficacy of physical activity interventions for older adults it is important to assess the effects of interventions on the specific areas of health that are important to older adults (e.g. functional capacity, well-being and social interaction). These areas were assessed using the following self-report questionnaires: the Positive and Negative Affect Schedule (PANAS) to assess mood [57]; the Short-Form (36) Health Survey version 2 (SF-36v2) questionnaire which measures quality of life [58]; the Perceived Motor-Efficacy Scale for Older Adults (PMES-OA) to assess functional ability [59]; and the UCLA Loneliness Scale (version 3) [60] as a measure of emotional and social loneliness. Questionnaires were completed by both groups at visits 1, 4 and 6. In addition to these questionnaires, at visit 1 participants completed a demographic questionnaire.

#### iii) Qualitative study

To gain an insight into participants' experiences of the walking intervention, two focus groups were conducted; one with the immediate group, the other with the delayed group (on completion of the 12-week programme). Focus groups are an established method for accessing personal experiences and for facilitating more in-depth understandings of participants' views [61]. All focus groups were facilitated by two members of the research team. Each group consisted of seven to nine participants and lasted for approximately an hour. Questions posed examined both positive and negative experiences. Specifically, the focus group schedule explored perceived benefits of increased walking, views on the pedometer, the physical activity consultation and on-going support, problems encountered, future recommendations and reflections on participation. Focus groups were audio-recorded, transcribed verbatim and thematically analysed (see below). These data, when combined with demographic and efficacy data, will provide insight into the mediators and moderators of change in walking behaviour. In addition, semi-structured interviews were conducted with key members of the research team, in order to explore their experiences of implementing the intervention. The interview schedule covered key questions about the feasibility of implementing the intervention into current care and other settings (including acceptability of intervention training to current general practice staff) and ways of improving the intervention for future delivery. The qualitative evaluation of the intervention supplements the experimental phase by providing context-rich, in-depth information on participants' experiences and provides an insight into the underlying processes that determine the feasibility of the intervention, for instance, what worked, what did not work, the perceived impact and why and how the intervention could be improved for future delivery.

### Setting

Visits were conducted either at a general practice in the West End of Glasgow or in the Glasgow Clinical Research Facility at the Western Infirmary, Glasgow (http://www.glasgowcrf.org.uk). Focus groups were conducted in a university building or a suitable community venue.

### Data management

Quantitative data were entered into a Microsoft Excel (Microsoft Corp., Redmond, WA, USA) database and stored on a secure network drive. All questionnaire data were double-entered and checked by a member of the research team. Qualitative data were audio-recorded, transcribed verbatim and anonymised. Hard copies of questionnaire data and the focus group and interview transcripts were kept in a secure filing cabinet.

### Data analysis

Data collection was completed in December 2010. Inferences about the effect of the intervention will be drawn from comparisons between groups in outcome measurements at baseline and at 12 weeks. Follow-up data at 24 weeks will be used in the immediate group to assess whether any benefits are maintained; in the delayed group follow-up data will provide a secondary assessment of the impact of the intervention. Data will be analysed on an intention to treat basis, that is according to the randomisation rather than whether or not the intervention was received or completed. In the first instance, missing data will not be imputed, though the sensitivity of the main findings will be assessed under alternative assumptions regarding missing values (such as last observation carried forward). Similarly, outlying values (e.g. very low step counts) will not be excluded from initial analyses, though analyses will be repeated following the exclusion of outcome values that fall outside plausible ranges. Qualitative data will be thematically analysed, which involves coding participants' speech into categories that summarise and systemise the content of the data [62]. NVivo 8 software (QSR International, Melbourne, Australia) will be used to aid coding and data retrieval.

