### Power Calculation

For the pilot element of this study, sample size was estimated based on the primary outcome measure, pedometer steps/day. Based on findings from previous work conducted by this research team a conservative estimate of the potential effect in this study was a mean increase of 2,000 steps/day [17]. From prior research [44,45], a conservative estimate of the standard deviation for steps/day in older adults is 3,000 steps. This corresponds to an effect size of *D *= .67 [46]. Additionally, pedometer counts from older adults have been shown to be highly reliable [44], thus a high correlation between baseline and post-intervention data can be expected. Using the Power and Precision software, sample size for a Repeated Measures ANOVA was calculated for *D *= .67, α = .05, an inter-trial correlation of *r *= .60, and a desired power of *β *= .80. This yielded a sample size of 16 participants per group. Assuming a 30% loss in follow-up, a sample size of 46 (23 per group) was agreed as the target.

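### The planned inference on steps/day is not fixed as a baseline-adjusted comparison, and the one model named (repeated-measures ANOVA) is less precise at the plan's own correlation

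*Protocol article*

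**What the plan says.** The Data analysis section of the protocol article states: "Inferences about the effect of the intervention will be drawn from comparisons between groups in outcome measurements at baseline and at 12 weeks". It adds that analysis follows the randomised allocation, that missing values are not imputed at first, and that the 24-week data serve secondary purposes. It names no statistical model for the 12-week comparison and does not mention baseline as a covariate, either to include it or to exclude it.

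A model appears only under Power Calculation, where "sample size for a Repeated Measures ANOVA was calculated". The inputs there are an effect described as "a conservative estimate of the potential effect in this study was a mean increase of 2,000 steps/day", a spread described as "a conservative estimate of the standard deviation for steps/day in older adults is 3,000 steps", a two-measurement correlation of 0.60, α of .05 and power of .80. The same section says of the pedometer's reliability: "thus a high correlation between baseline and post-intervention data can be expected". The result is 16 per group, raised to 23 per group for 30% loss.

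Under Outcome measures, pedometer data are collected between visits 1 and 2 as the baseline reading for both groups.

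**The concern.** When each participant has one baseline and one 12-week value, the group-by-time test of a repeated-measures ANOVA is the same test as a two-sample t-test on the change from baseline. A change score subtracts the whole baseline value, which is right only if the regression of follow-up on baseline has slope 1. With equal standard deviations and a correlation of 0.60 the slope is 0.60, so the change score subtracts too much. The excess adds noise to the estimate and ties it to whatever baseline difference chance has produced.

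The article reports an intention to use baseline but leaves open how, and the one model it names is the less efficient way. The trial is planned around 16 completers per group, and the Strengths section says its findings decide whether a larger trial should follow and cites safe assumptions about effect size and variability as an objective. Precision that costs nothing is worth having in that setting.

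**Working it through.** **Inputs (Power Calculation section).** Effect δ = 2,000 steps/day; SD σ = 3,000, taken as equal at both times; correlation r = 0.60; α = .05, assumed two-sided because the article does not say; n = 16 per group before loss, 23 after.

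**The plan's own figure.** The inflation for loss reproduces: 16/(1 − 0.30) = 22.9, so 23 per group. The 16 itself does not reproduce as a between-group test of change. The change-score SD is 3,000 × √(2 × 0.40) = 2,683, which needs 29 per group by the normal approximation and 30 by the t distribution. The 16 is close to a within-group before–after test (paired t, power 79.6% at n = 16). That is a separate matter; here 16 and 23 serve only as the planned numbers.

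**Variance of each analysis, as a multiple of 2σ²/n.**
- Change score: 2(1 − r) = 0.80.
- 12-week value adjusted for baseline, large sample: 1 − r² = 0.64.
- Ratio: (1 − r²)/[2(1 − r)] = (1 + r)/2 = 0.80, a 20% reduction.

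**Small-sample cost of estimating the slope.** With a normally distributed baseline, the adjusted estimate's variance is multiplied on average by 1 + 1/(2n − 4).
- n = 16: 1 + 1/28 = 1.036, so the ratio is 0.80 × 1.036 = 0.83, a 17% reduction.
- n = 23: 1 + 1/42 = 1.024, so the ratio is 0.82.

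**Standard errors at n = 16.**
- Change score: 2,683 × √(2/16) = 949 steps/day.
- Adjusted: 3,000 × √0.64 × √(2/16 × 1.036) = 864 steps/day, about 9% smaller (864/949 = 0.91).

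**Power for 2,000 steps/day (noncentral t, two-sided .05, averaging over the chance baseline difference for the adjusted analysis).**

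| Completers per group | Change score | Adjusted for baseline |
|---|---|---|
| 16 | 0.53 | 0.61 |
| 23 | 0.70 | 0.78 |

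A simulation at 16 per group agreed closely, and both estimates averaged about 2,000.

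**Range over r.** The article gives one value, so 0.4 to 0.9 is an assumed range. The table is for n = 16.

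| r | Large-sample ratio (1 + r)/2 | Ratio × 1.036 |
|---|---|---|
| 0.4 | 0.70 | 0.73 |
| 0.6 | 0.80 | 0.83 |
| 0.8 | 0.90 | 0.93 |
| 0.9 | 0.95 | 0.98 |

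The advantage disappears at n = 16 when (1 + r)/2 × 29/28 = 1, that is at r = 0.93.

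**Chance baseline difference.** One standard error of the baseline difference at n = 16 is 3,000 × √(2/16) = 1,061 steps/day. Given a difference of that size, the expected change-score estimate is off by −(1 − 0.60) × 1,061 = −424 steps/day, about a fifth of the target effect (424/2,000 = 0.21). The minus sign shows over-correction. The adjusted estimate has no such error in expectation.

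**The case against.** The strongest reply is that the article does not plan the analysis being criticised. The Data analysis section names no model; repeated-measures ANOVA is only the basis of the sample size; and the inference sentence identifies the arms, the time points and the randomised period in words that also fit a baseline-adjusted model. The model form and covariates usually belong in an analysis plan, which is not shown. This stands to the extent that it would be wrong to say that the trial will use change scores or has rejected adjustment. It does not dispose of the point, because the article does describe its inferential comparison, and the one model it names points to the less precise method.

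A reader might also infer more than the text supports:
- **That baseline differences will be significance-tested.** The section speaks of comparisons at both times but describes no such test.
- **That 12-week values alone will be compared, with a 36% variance loss (1 − 0.64).** The inference sentence and the power calculation both bring baseline in, so this is not the likely plan.
- **That randomisation is simple and unstratified.** The Procedures section describes one-to-one allocation by sealed envelope and is silent on blocking and stratification.
- **That the estimate would be biased.** Both estimators are unbiased over randomisations; the error shown is conditional on an observed imbalance.

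Two further objections limit the size. The gain shrinks as the correlation rises, and the article expects a high one. The 1,061-step figure uses the full SD of 3,000, whereas anyone at 70,000 or more steps in the baseline week is excluded, so the true baseline spread may be narrower.

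**Conclusion.** The point holds as a recommendation on efficiency. The article leaves the 12-week comparison without a stated baseline-adjusted model, and the only model it names amounts to a change-score test. On the plan's inputs, baseline adjustment has about 17% less variance than that test at 16 per group (20% in large samples) and raises power from about 0.53 to 0.61. It also protects the estimate against a chance baseline difference that a change score over-corrects.

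These figures assume equal SDs of 3,000 at both times, r = 0.60, a two-sided test and roughly normal data. The gain is larger at lower correlations and nearly gone by r = 0.9. A repeated-measures ANOVA would still be valid and unbiased, and the documents do not support calling the plan wrong or saying that adjustment has been ruled out.

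**What to change.** Add one sentence to the Data analysis section, or to the analysis plan if one exists: the primary analysis is a linear model of 12-week steps/day on randomised group with baseline steps/day as covariate, reported as the adjusted mean difference with its 95% CI. The equivalent mixed model, with a common baseline mean for both groups and a group effect at 12 weeks, is also suitable. Analyse each secondary outcome the same way with its own baseline value.

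The cost is that sentence and one degree of freedom. Baseline is already measured in both groups before the intervention starts, so no further data are needed, and the article still describes the analysis in the future tense.
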